## 4.8 Sample size

In accordance with the main objective of the larger study, the sample size estimate is designed to detect changes in the proportion of skilled delivery service utilization. The sample size is calculated using stata software based on the following assumptions. Tail (s): One; effect size (d): 0.15; **α** error probability = 0.05; power (1-**β** error probability) = 0.8, and allocation ratio (N1/N2) = 1. This gives a sample size of 155. Then, adding design effect, DE = 1+(m-1)ICC , where m=Average cluster size, m= 50, ICC=0.02 based on a published study ICC (Killip et al., 2004), DE=2, and allowing for a 10% loss to follow up, the total sample size is 682 (N1 = 341 and N2 = 341). N1 and N2 are sample sizes in the control and intervention group, respectively. Based on these assumptions, the estimated sample size is: 306 pregnant mothers per group to detect a 15-percentage point anticipated difference in the proportion of skilled delivery service utilization (an increase from 26% to 41%). This estimate is based on the baseline skilled delivery service utilization in the Ethiopia Demographic and Health Survey (26% from EDHS 2016, SNNP region report) in the control group (CSA, 2016).

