Knowledge of danger signs during pregnancy has 14 items, Knowledge of danger signs of labor and childbirth has 9 items and knowledge of neonatal danger signs has 11 items. All Knowledge score will be computed by adding the total number of correct spontaneous responses to maximum number of items with a minimum score of 0 and maximum of number of items (0 when a mother mentioned none of the key danger signs and maximum number when the mother mentioned all the danger signs). Spontaneous response is respondents’ naming of danger signs without giving option of the respective signs. Accordingly, two categories will be developed for knowledge of danger signs (Good and poor categories). Women who mention at least three neonatal danger signs will be considered to have good knowledge whereas those who mentioned less than three of the danger signs will be labelled to have poor knowledge as stated by several studies. Questionnaire on BPCR is adopted and modified from monitoring BPCR tools for maternal and new-born health (Maternal, 2004). Attitude towards skilled delivery service utilization has 12 items that will be measured by using Likert scale where respondents are supposed to strongly agree, agree, neutral, disagree and strongly disagree. The overall attitude score will computed by summing up the items after performing the reverse scoring for negatively worded sentences. A higher composite score indicated a more favourable attitude.

*Perception of Pregnancy Risk Questionnaire (PPRQ****)*** was developed by Heaman and Gopton (Heaman and Gupton, 2009). It is a self-report questionnaire consisting of 9 visual analogue scales designed to measure a pregnant woman’s perception of her pregnancy risks. This questionnaire consists of two subscales that include four questions about the risk to self (mother), (for example “is a risk of having a cesarean section”); and five questions about risk to the baby, (for example “is a risk of baby having a birth defect”). “Respondents will be asked to put a vertical mark through the line to indicate their assessment of risk for each Item,” (yielding a score ranging from 0-100). A total PPRQ score will be obtained by adding the score for each of the 9 items, and then dividing by 9, to obtain a score out of 100. Higher scores will indicate higher levels of perceived risk.

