## 4.17 Data collection and management

The principal investigator will train the data collectors and supervisors for two
consecutive days on instruction; in the quantitative method, study guides, role-plays
(demonstration), informed consent, how to approach participants, how to collect data using
mobile health, ethical procedure and general information and the objective of
the study. The data will be collected by using a mobile-based application called open data kit
(ODK). In the initial step, a pre-intervention survey will be conducted after the randomization and allocation. And there will be two times data collection including the pre-intervention and post-intervention data. The data will be collected by 4 months interval to have a good longitudinal data. The type of data will be panel data with repeated cross-sectional. Experienced data collectors with health background and Hadiyisa speaking will be recruited to collect the data. Besides, a master holder with health profession will be employed to supervise the whole data collection process.

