## 4.19 Statistical analysis

Data of baseline and end-line surveys will be combined and analyzed using Stata 14.1. Analyses will be based on the intention-to-treat principle and compared differences of the outcomes between the intervention and control at both individual and cluster levels. First, Univariate analyses will be performed to explore the characteristics of respondents. We then will use logistic regression with random effects to estimate the effect of the intervention on prenatal behaviour, adjusting for clustering. Generalized estimated equations (GEE) regression analyses adjusted for clustering will be used to test the effect of the intervention on promoting maternal health behaviour. We will repeat analyses for the primary and secondary outcomes adjusted for baseline differences by fitting an interaction term between study period (baseline vs intervention) and allocation in each model. Mixed-effects multilevel logistic regression model will be used to identify determinants of birth preparedness and complication readiness.

**For qualitative study:** The interviews will be recorded and transcribed verbatim. The transcripts will be thematically analyzed using the qualitative software program Atlas.ti 6.0. Two analysts will independently code the transcripts and subsequently review, discuss, and refine the coding schemes until consensus will be reached. Emerging concepts will be assessed using the constant comparative method from grounded theory. This means that when this concept will be identified, previously analyzed interviews will be reviewed in order to check if their content fitted into this concept. A final version of the code book will be then developed leading to identification of themes, and sub-themes. Coded transcripts will be further analyzed and summarized in narratives for each theme and sub-theme. Study findings will be presented, discussed, and validated in a stakeholder meetings conducted in regional and district health offices.

| S.no | Research objectives | Study populations | Study design | Data source | Major outcome variables | Analytic model |
| --- | --- | --- | --- | --- | --- | --- |

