# APPENDICES

# **Annex 1: Questionnaire** for quantitative part

D**eveloped to collect baseline and end-line data for the project entitled** Effectiveness of trained religious leaders’ engagement in maternal health education on maternal health service utilizations: Evidence from cluster randomized controlled trial study in Misha District, Hadiya Zone, and Southern Ethiopia

General Information

Name of Kebele: ________________

Name of Gote __________________

House number ____________________

Family Id ____________________

Individual Id __________________

Date of interview: ____________time interview started _____________ ended at ____________

Respondent available on: 1. 1st visit.

2^nd^ visit.

3^rd^ visit.

Status of interview: 1. Completed. 2. Partially completed (refused in the middle).

Refused: 4. Candidate was absent in 3 visits:

11. Interviewer‘s name: --------------------------------------------Signature: -------------------

12. Supervisor who checked questionnaire for completeness and accuracy:

Name: --------------------------------------------Signature: -------------------------

Date-------------------------

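### No model in section 4.19 conditions on baseline knowledge of danger signs (Objective 1), although it is collected; the only baseline adjustment is a period-by-allocation interaction, which is less precise

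*Protocol*

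**What the plan says.** Section 4.19 (Protocol) combines the two surveys and names random-effects logistic regression. It then states: "Generalized estimated equations (GEE) regression analyses adjusted for clustering will be used to test the effect of the intervention". The summary table at the end of that section assigns GEE to Objective 1. The analyses are then to be repeated, "adjusted for baseline differences by fitting an interaction term between study period (baseline vs intervention) and allocation in each model". No listed model names a baseline value as covariate.

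Knowledge has a baseline value. Section 4.16 defines it: "All Knowledge score will be computed by adding the total number of correct spontaneous responses". There are three separate scores: pregnancy (14 items), labour and childbirth (9) and neonatal (11). The Annex 1 questionnaire was developed "to collect baseline and end-line data for the project entitled". It carries an individual ID, and its Part V asks about danger signs.

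The protocol does not settle whether the same women are interviewed twice. The Summary and section 4.11 describe repeated cross-sectional surveys. Section 4.17 says "The type of data will be panel data with repeated cross-sectional". Enrolment before 20 weeks (4.5), an end-line interview one month after delivery (4.17) and a 10% allowance for loss to follow-up (4.8) point to a cohort.

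**The concern.** Skilled delivery and antenatal attendance in the index pregnancy have no comparable value at enrolment; knowledge does. With only 12 kebeles, chance differences in baseline knowledge between arms can be sizeable. The clustering-only GEE leaves in the estimate whatever part of that difference persists. The interaction compares changes, so it removes the whole difference even though only part of it would have persisted. The two analyses can therefore err in opposite directions on the same data, and both use the baseline less efficiently than a model that conditions on it. What is at stake is the precision of Objective 1 and its sensitivity to chance imbalance.

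**Working it through.** **Inputs from section 4.8.** They are written for skilled delivery; none are given for knowledge. "Tail (s): One; effect size (d): 0.15", alpha "error probability = 0.05", power and allocation "error probability) = 0.8, and allocation ratio (N1/N2) = 1"; rates 26% and 41%; ICC 0.02 with 50 women per kebele; 306 women per arm. Section 4.11 gives 6 kebeles per arm. The design effect is 1 + 49 × 0.02 = 1.98.

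**The plan's own figure.** The pooled two-proportion formula at two-sided 5% and 80% power gives 154.2, so 155 per arm, as stated. The one-tailed test that the section names gives 121.4, so 122. The stated size thus corresponds to a two-sided test, which is used below. 155 × 1.98 = 306.9, which accounts for 306; 155 × 2 × 1.1 = 341.

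**End-line-only power.**
- Variance of the arm difference = (0.26 × 0.74 + 0.41 × 0.59)/306 × 1.98 = 0.002810; SE = 0.0530.
- 0.15/0.0530 = 2.83; power = Φ(2.83 − 1.96) = 81%.
- This takes the clustering-only GEE as an end-line comparison.

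**Relative variances.** Let R be the correlation of kebele means between surveys, with equal variances at the two surveys. Multiply the variance above by 1 (end line only), 2(1−R) (period by allocation) or 1−R² (baseline as covariate). Since 2(1−R) − (1−R²) = (1−R)², the covariate model is never less precise than the interaction. Since 1−R² ≤ 1, it is never less precise than end line only. The interaction beats end line only when R exceeds 0.5 and loses when R is below 0.5.

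**Power at assumed R** (two-sided 5%, normal approximation):

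| R | End line only | Interaction | Baseline covariate | Gain over interaction | Gain over end line only |
|---|---|---|---|---|---|
| 0.3 | 80.8% | 66.7% | 84.3% | 17.6 | 3.5 |
| 0.5 | 80.8% | 80.8% | 90.4% | 9.7 | 9.7 |
| 0.6 | 80.8% | 88.6% | 94.3% | 5.7 | 13.5 |
| 0.7 | 80.8% | 95.5% | 97.7% | 2.3 | 17.0 |
| 0.8 | 80.8% | 99.4% | 99.7% | 0.3 | 18.9 |

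With t reference distributions (10 df; 9 df for the covariate model), power at R = 0.5 is 72%, 72% and 83%.

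**What R could be.** R = [CAC × ICC + r(1−ICC)/m] / [ICC + (1−ICC)/m]. Here CAC is the correlation of the kebele effects between surveys and r the within-woman correlation; both are assumptions. With ICC 0.02 and m = 50:
- Different women (r = 0): R = 0.25, 0.40 and 0.51 at CAC 0.5, 0.8 and 1.0. The gain over the interaction is about 19, 14 and 9 points; over end line only, about 2, 6 and 10.
- Same women with r = 0.5: R = 0.50, 0.65 and 0.75 at the same CAC values. The gain over the interaction is about 10, 4 and 1 points; over end line only, about 10, 15 and 18.

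**Chance imbalance.** The SD of the baseline arm difference is √(2 × 0.26 × 0.74/306 × 1.98) = 0.050, or 5.0 percentage points. At R = 0.5, a 1-SD imbalance leaves 0.5 × 5.0 = 2.5 points in the end-line-only estimate. The interaction over-subtracts (1 − 0.5) × 5.0 = 2.5 points in the other direction. The section 4.8 target is 15 points.

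**The case against.** Several objections stand.
- **Same women or not.** A reader might infer that each woman certainly has a before and an after score. The protocol does not support that: it calls the surveys repeated cross-sectional, replaces women who are absent at baseline, and repeats the same procedure at end line. If the women differ, only a kebele-level baseline is available, and stacking the surveys with an interaction is a conventional analysis.
- **Size.** A reader might infer a fixed loss of 5 to 17 points. That range needs R of roughly 0.3 to 0.6. R is a correlation of kebele means, not of a woman's own scores. At R of 0.7 or above the gain over the interaction is under 3 points.
- **Role of the interaction.** It is a repeat analysis, not the test listed for Objective 1, so its power loss does not by itself fall on that test.
- **Selection.** Section 4.17 places the baseline survey after allocation, and section 4.15 describes a public allocation. Imbalance may then reflect recruitment as well as chance, and a change comparison removes stable differences. This is a reason to keep the interaction as a sensitivity analysis.
- **Scope.** A reader might extend the point to the attitude score. Section 3.2 does not make attitude an outcome of Objectives 1 to 3, so it is left out.

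One objection does not carry. The Summary calls the GEE model multivariable, and covariate lists can be left to an analysis plan. But section 4.19 does fix how baseline differences are to be handled, and its method is the interaction.

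**Conclusion.** The point holds as a matter of efficiency and of robustness to chance imbalance; the planned analyses are not invalid. Under the variance model above, conditioning on baseline knowledge is at least as precise as either planned analysis for any R from 0 to 1. When R is low the gain is mainly over the interaction; when R is high it is mainly over the clustering-only GEE. At R = 0.5 it is about 10 points over both.

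The direction does not depend on whether the women are the same; the size does. The figures rest on an assumed R, on rates and an effect borrowed from skilled delivery, and on a linear approximation to a logistic model. With a kebele-level covariate and R near zero, the lost degree of freedom would cost about 1 point of power.

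**What to change.** 1. Reconcile the Summary and sections 4.11 and 4.17 on whether the same women are interviewed at both surveys.
2. In section 4.19, make the main Objective 1 model the end-line knowledge outcome on allocation, accounting for clustering by kebele, with baseline knowledge as covariate. If women are linked, use the woman's own baseline score for the corresponding period, since section 4.16 defines separate scores. If they are not, use the kebele's baseline mean or proportion.
3. Report a standardised risk difference or ratio, so that adding the covariate does not change what the estimate means.
4. Keep the period-by-allocation model as a sensitivity analysis, because the baseline survey follows allocation.

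The cost is a change of wording, with no new data or visits. It requires linking forms by the individual ID already on the questionnaire, a rule for missing baseline scores, and one degree of freedom if the covariate is at kebele level.

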## 3.2 Specific objectives

**Objective 1**: To assess effectiveness of trained religious leaders’ engagement in maternal health education in improving knowledge and recognitions of danger signs during pregnancy and child birth.

**Objective 2**: To assess effectiveness of trained religious leaders’ engagement in maternal health education on antenatal care service utilization

**Objective 3**: To assess effectiveness of trained religious leaders’ engagement in maternal health education on skilled delivery service utilization

**Objective 4**: To develop and validate religious’ leaders maternal health education engagement scale: elicitation study on mothers’ perception on religious leaders based maternal health promotion then scale development

**Objective 5**: To explore perception of religious leaders in promoting maternal and child health in rural setting.

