## 4.2 Study design

This study is a cluster randomized control trial to assess effectiveness of trained religious leaders’ engagement in maternal health education on maternal health behaviours. A total of five objectives will be answered from this study. Objectives 1, 2 and 3 are designed as a community-based cluster randomized control trial, which evaluates the effectiveness of trained religious leaders’ engagement in maternal health education on maternal health behaviours (ANC, SDS and knowledge of danger signs during pregnancy and child birth)**.** The fourth objective is designed as a cross-sectional study for the scale validation on engagement of religious leaders in promoting maternal health; the survey will assess how effectively the religious leaders deliver maternal education, to estimate dimensions of engagement. The fifth objective is qualitative study, designed as explorative grounded theory.

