## 4.18 Data Quality Control

To assure the quality of the data, data collectors and supervisors will be trained and a regular supervision and follow-up will be made by supervisors and the principal investigator. In addition, a regular check-up for completeness and consistency of the data will be made on daily basis. The questionnaire is translated into Amharic language and back-translated into English by translators who are blind to the original questionnaire. To make the questionnaire standard, reliability and validity test will be done for scale variables. Pilot test and Pre-test of the tool will be carried out in the area which has similar characteristics with the study population in Anlemo district will be done before two weeks of the actual data collection to ensure clarity, wordings, logical sequence and skip patterns of the questions. The pre-tested sample will be not included in the study and modification will be made.

For the qualitative study: Silent and comfortable places and convenient times will be selected and arranged to conduct, in-depth interview with religious leaders so as to allow maximum concentration. Study participants will also be made to give a true answer through explaining the purpose and importance of the study and assuring the confidentiality of data they are going to provide. To enhance inter-coder reliability, the coders each will independently apply the code book to a selected and rich transcript and review any differences in their coding, which will be discussed and resolved.

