| 1 | To assess effectiveness of trained religious leaders’ engagement in maternal health education on knowledge of danger signs during pregnancy and child birth | Pregnant mothers | Cluster randomized control trial | Household survey | knowledge of danger signs during pregnancy and child birth | Generalized estimated equations (GEE) regression analyses |
| 2 | To assess effectiveness of trained religious leaders’ engagement in maternal health education on antenatal care service utilization | Pregnant mothers | Cluster randomized control trial | Household survey | antenatal care service utilization | Generalized estimated equations (GEE) regression analyses |
| 3 | To assess effectiveness of trained religious leaders’ engagement in maternal health education on skilled delivery service utilization | Pregnant mothers | Cluster randomized control trial | Household survey | skilled delivery service utilization | Generalized estimated equations (GEE) regression analyses |
| 4 | To develop and validate religious’ leaders maternal health education engagement scale: elicitation study on mothers’ perception on religious leaders based maternal health education then scale development | Pregnant mothers | Cross-sectional study | Household survey | Religious leaders engagement in maternal health education | exploratory factor analysis |
| 5 | To explore role of religious leaders in promoting maternal and child health: a religious leaders’ view in rural setting of Hadiya Zone, Southern Ethiopia.  **Research questions:**   1. Do religious leaders address the topic of maternal health in their contacts with members of their congregations? If so, when and how do they address the topic? 2. To what extent religious leaders willing to enter into a dialogue with authorities on the topic of maternal health? | Religious leaders | Grounded theory | In-depth interviews and FGDs among religious leaders | NA | Thematic analysis |

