**Part IX Religious leaders’ engagement scale measurement tool (end-line)**

| 801 | My religious leader was consistent reminder so that I keep ANC follow up based on schedule or appointment | 1. Strongly disagree; 2. Disagree; 3.Neutral; 4. Agree; 5. Strongly agree |  |
| --- | --- | --- | --- |
| 802 | My religious leaders frequently reminded to complete taking iron-folate without interruption | 1. Strongly disagree; 2. Disagree; 3.Neutral; 4. Agree; 5. Strongly agree |  |
| 803 | My religious leaders repeatedly notified us about tetanus toxoid vaccination | 1. Strongly disagree; 2. Disagree; 3.Neutral; 4. Agree; 5. Strongly agree |  |
| 804 | My religious leaders repeatedly notified us about STI and HIV screening and counselling | 1. Strongly disagree; 2. Disagree; 3.Neutral; 4. Agree; 5. Strongly agree |  |
| 805 | My religious leaders commonly prompted us in identifying skilled provider | 1. Strongly disagree; 2. Disagree; 3.Neutral; 4. Agree; 5. Strongly agree |  |
| 806 | My religious leaders commonly encouraged us to give birth at health facility | 1. Strongly disagree; 2. Disagree; 3.Neutral; 4. Agree; 5. Strongly agree |  |
| 807 | My religious leaders commonly encouraged us to prepare transportation during labor | 1. Strongly disagree; 2. Disagree; 3.Neutral; 4. Agree; 5. Strongly agree |  |
| 808 | My religious leaders commonly encouraged us to identify sources of support for me and my family during the birth and the immediate postnatal period | 1. Strongly disagree; 2. Disagree; 3.Neutral; 4. Agree; 5. Strongly agree |  |
| 809 | My religious leaders commonly encouraged us to prepare any additional costs associated with the birth, preparing supplies for my care and the care of my new-born baby. | 1. Strongly disagree; 2. Disagree; 3.Neutral; 4. Agree; 5. Strongly agree |  |
| 810 | My religious leaders repeatedly notified us about danger signs during pregnancy | 1. Strongly disagree; 2. Disagree; 3.Neutral; 4. Agree; 5. Strongly agree |  |
| 811 | My religious leaders repeatedly notified us about danger signs during labour and child birth | 1. Strongly disagree; 2. Disagree; 3.Neutral; 4. Agree; 5. Strongly agree |  |
| 812 | My religious leaders repeatedly notified us about danger signs during post-partum period | 1. Strongly disagree; 2. Disagree; 3.Neutral; 4. Agree; 5. Strongly agree |  |

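### Objective 4 promises a validated engagement scale, but the only model named is an exploratory factor analysis of one survey, which supports development, not validation

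*Protocol*

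**What the plan says.** Section 3.2 gives Objective 4 as "To develop and validate religious’ leaders maternal health education engagement scale", with an elicitation study of mothers' perceptions before scale development. Section 4.2 states: "The fourth objective is designed as a cross-sectional study for the scale validation on engagement of religious leaders in promoting maternal health". The same sentence gives the survey's purpose as "to estimate dimensions of engagement".

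The design summary table in section 4.19 repeats the promise to develop and validate. For this objective it lists a cross-sectional design, a household survey as data source, and one analytic model: "exploratory factor analysis". The narrative of section 4.19 says nothing about Objective 4.

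Section 4.18 contains one further commitment: "To make the questionnaire standard, reliability and validity test will be done for scale variables". It then describes a pilot and pre-test in another district to check clarity, wording, sequence and skip patterns, and adds: "The pre-tested sample will be not included in the study and modification will be made".

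The engagement tool is Part IX of Annex 1. It has 35 numbered items (801 to 835) in the English form, and its heading marks it as an end-line instrument.

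**The concern.** Developing a scale and validating it are different tasks. An exploratory factor analysis uses the answers to decide how many dimensions there are and which items belong to each. Validation then asks whether that fixed structure holds in answers that played no part in choosing it, or whether the score behaves as it should against something outside the scale. The protocol promises both tasks and names a model only for the first.

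At stake is what may be concluded about the scale. If the plan is followed as written, the report could call the scale validated and others could reuse it, with no evidence that its dimensions replicate.

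The items add a particular difficulty. Most ask what the woman's religious leaders did about maternal health, which is what the intervention sets out to change in one arm only. The protocol does not say whether the arms are pooled for Objective 4.

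**Working it through.** The protocol states no sample size, power or error rate for Objective 4, so there is no figure to reproduce. The check compares passages, with two calculations on what an exploratory analysis can and cannot show.

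**1. Promise against method.**

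| Place | What it commits to |
|---|---|
| 3.2 and summary table in 4.19 | Develop and validate |
| 4.2 | Cross-sectional study for validation; aim is to estimate dimensions |
| 4.19, summary table | Exploratory factor analysis, one household survey |
| 4.18 | Reliability and validity test for scale variables; no method, sample or criterion |
| 4.18, pre-test | Wording and flow; those women are excluded from the study |
| Annex 1, Part IX | Tool marked as end-line |

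No confirmatory model, second or held-out sample, or external criterion is stated. The pre-test cannot serve as the second sample, because its stated purpose is wording and flow and the tool may be modified afterwards.

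**2. Can an exploratory analysis expose items that do not cohere?** Yes. Inputs: 35 items (Annex 1, Part IX), answered at random on five points and mutually unrelated. Sample sizes are 341 and 682 (the per-arm and total recruitment figures in section 4.8, assumed here because none is given for Objective 4), with 500 simulated data sets each.

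- Mean Kaiser-Meyer-Olkin sampling adequacy: 0.47 and 0.49.
- Bartlett's test significant: 6.4% and 5.6% of data sets.
- Parallel analysis kept at least one factor: 5.8% and 4.2%.
- In separate runs at 306 and 612 women, Cronbach's alpha averaged about 0.

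Ordinary checks would therefore usually flag unrelated items.

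**3. Can those checks be passed for the wrong reason?** Yes, if the arms are pooled. Assume two equal arms, items unrelated within each arm, and every item shifted by d within-arm standard deviations between arms. The values of d are assumptions.

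- Correlation between any two items in the pooled data: r = (d²/4) / (1 + d²/4).
- Cronbach's alpha for 35 items: 35r / (1 + 34r).
- First eigenvalue: 1 + 34r.

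| d | r | alpha | First eigenvalue |
|---|---|---|---|
| 0.5 | 0.0625/1.0625 = 0.059 | 2.059/3.000 = 0.69 | 3.0 |
| 0.8 | 0.16/1.16 = 0.138 | 4.828/5.690 = 0.85 | 5.7 |
| 1.0 | 0.25/1.25 = 0.200 | 7.0/7.8 = 0.90 | 7.8 |

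Simulation with 612 women agrees: alpha 0.67, 0.84 and 0.89; sampling adequacy 0.69, 0.89 and 0.94; parallel analysis kept a factor in every data set. A factor with good reliability can thus reflect arm membership alone. A random split within kebele would reproduce it in both halves, so the structure must also be examined within each arm.

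**The case against.** The strongest reply has four parts.

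- **Section 4.18 does commit to testing.** It promises a reliability and validity test for scale variables, in a sentence separate from the one on the pre-test. This stands: it would be wrong to say that exploratory factor analysis is the only analysis mentioned. But the sentence covers all scale variables, is aimed at standardising the questionnaire, and names nothing that would test this scale's structure.
- **Development work is planned.** The elicitation study contributes to content validity, and exploratory analysis suits the aim of estimating dimensions. This also stands, and it supports calling the objective development.
- **The summary table is brief, and detail may sit in a statistical analysis plan that is not shown.** Retention rules, fit limits and the reliability statistic can reasonably be left there, and their absence is not the point. The point is that the protocol names a model and attaches to it a promise of validation that the model does not meet.
- **Exploratory analysis is not empty.** A reader might infer that it cannot fail and would give much the same result on unrelated items. With an eigenvalue-above-1 rule on the full correlation matrix, pure noise does yield about 16 components. But that is principal components with a retention rule, and the protocol names neither. On the same kind of noise, common-factor extraction with that rule kept essentially none (0.003 on average at 306 women, 0 at 612), and the checks in the working would usually raise the alarm. The stronger reading is not supported.

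**Conclusion.** The point holds in a limited form. The protocol promises to develop and validate the scale, names one exploratory model on one survey, and adds an unspecified reliability and validity test. On that plan the trial could report a proposed structure and its reliability. It could not conclude that the scale is validated, because nothing stated tests the structure in data not used to find it.

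Severity is minor. Objective 4 stands apart from the randomised comparison, and Objectives 1 to 3 are unaffected. No numerical error is claimed. The warning about arms assumes that both arms are pooled and that the intervention shifts the answers; the protocol settles neither.

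**What to change.** Amend sections 3.2 and 4.2 and the summary table in section 4.19 in one of two ways.

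1. **Reword.** State Objective 4 as scale development only and remove the references to validation. This changes a few words and costs nothing else.
2. **Add the validation step.** Split the scale sample once, at random within kebele. Use one half for the exploratory analysis, with the number of factors set by parallel analysis. In the other half, fit a confirmatory factor analysis of that fixed structure, with fit limits stated beforehand, and report reliability. Check the structure within each arm, since a difference between arms alone can produce a factor.

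The second route needs no additional women. Each half would hold about 306 women if 612 are analysed (2 × 306, section 4.8), or 341 if all 682 are, and fewer within each arm. A random half of the same kebeles is only an internal check, so the report should not claim validation beyond this setting. Number of sessions attended should not be used as an external criterion: control women receive no sessions, so it would largely re-measure arm, and the intervention table in section 4.13 lists only the percentage of mothers who took part.
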